## Discussion

The nature of the study overall, the study population, and the study design necessitates co-operation from and collaboration among the LTC administrative and health care staff, family members, family physicians and research personnel. Early involvement of key stakeholders, frequent communication and updates, as well as timely responsiveness to issues and concerns are critical to the success of this study. Implementing a walking intervention study in a population with varying degrees of cognitive and physical impairments who reside in LTC is not without its challenges. The large majority of the individuals to be recruited will present with some level of cognitive impairment. Numerous studies have led to the conclusion that people with moderate cognitive impairments (defined as Mini Mental Status Examination [56] scores of 12/13) are able to respond consistently to questions about choices and their involvement in decisions about daily living [57-60]. However, some residents will have cognitive impairments that are so severe that they cannot provide informed consent to participate in the study. An additional step in the recruitment protocol then has been to obtain proxy consent from a designated substitute decision maker or in the cases where capacity to consent is not clear, obtain both resident and proxy consent. Meeting with the LTC staff to discuss the study is an important first step, as the staff being asked to identify potential/eligible participants and assess residents to determine if potential participants are capable of providing informed consent. Obtaining consent and consent processes can be lengthy and difficult, even with individuals without cognitive impairments, and with our study population we have an additional layer of complexity to the study procedures. Not only do cognitive impairments affect the consent processes, but difficulty with data collection, in particular with those with severe impairments, is expected.

We initially structured the walking intervention to be comprised of two 30-minute walks per day, but quickly realized that the feasibility of this approach would not work in the participating LTC facilities. Long-term care facilities, by nature, have limited organizational flexibility with structured times for meals, activities, medication administration, vitals checks and so on, which limits the amount of time to engage the participants in the intervention. These conflicting daily activities provide a very narrow window of opportunity for many aspects of the study, including obtaining consent, baseline assessments and re-assessments and intervention implementation. Additional LTC contextual and environmental factors, including staff-to-resident ratios, caseload mix, organization of services, research readiness, staffing shortages, and viral outbreaks have all impacted on the study procedures and day-to-day implementation.

A considerable amount of time spent on Research Assistant (RA) training and standardization to ensure the walking intervention is safe, effective and similar among the RAs who are hired for the walking intervention.

Interaction and communication with individuals with cognitive impairments are important considerations for conducting study assessments and carrying out the interventions. Creating a personal connection with the individual; using appropriate facial expressions, eye contact, and tone of voice; using one-step commands; and, incorporating appropriate and consistent cueing in a progressive manner (e.g., verbal and visual cueing), demonstration, tactile guidance, and if necessary, physical assistance are useful strategies that have been reported in the literature and that need to be incorporated into the assessment and intervention protocols. Evaluators and research staff need to be trained in these strategies in order to maximize the success of interactions, and to ensure consistency of testing procedures and intervention implementation. Because the research sites include several LTC facilities, RA scheduling is a challenge. Intermittent quarantining of facilities due to outbreaks further challenges research staff to supply consistent interventions. Last, because of the length of the study, RA turnover because of competing academic and career priorities necessitates much time to be spent on quality control.

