**Methods/design:**

We are randomly assigning residents of long-term care facilities into one of three intervention groups: (1) *Usual Care Group* - individuals receive care as usual within their long-term care unit; (2) *Interpersonal Interaction Group* - individuals receive a comparable amount of one-on-one stationary interpersonal interaction time with study personnel administering the walking program; and, (3) *Walking Program Group* – individuals participate in a supervised, progressive walking program five days per week, for up to half an hour per day. Assessments completed at baseline, 2 and 4 months during intervention, and 2 and 4 months post-intervention include: gait parameters using the GAITRite® computerized system, grip strength, the Berg Balance Scale, the Senior Fitness Test, the Older Adult Resource Services Physical Activities of Daily Living, the Geriatric Depression Scale Short Form, the Cornell Scale for Depression in Dementia, the Revised Memory and Behavior Problems Checklist, the Short Portable Mental Status Questionnaire, the Coloured Analogue Scale, pain assessment scales, and the number and nature of falls. Sophisticated data analytic procedures taking into account both the longitudinal nature of the data and the potential for missing data points due to attrition, will be employed.

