### Sample size

Sample size calculations assumed a moderate standardized effect size of 0.40 [28], a small value for the intra-class correlation (i.e., the proportion of variation accounted for by LTC units) of 0.05, and α = .05, power = .80. Sample size calculations determined that a sample size of 129 total participants will provide ample power for repeated measures analyses [29]. A balanced design will be adopted, with equal numbers of participants in each group. We will collect data from an additional 50 participants in order to account for attrition due to refusal or inability to continue with the protocol. As well, morbidity and mortality may account for some attrition.

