(5) Cornell Scale for Depression in Dementia (CSDD). We are assessing depression using the CSDD, a well-validated scale, with high sensitivity [40,41], and high inter-rater reliability and internal consistency [41]. The CSDD is designed for the assessment of depression in individuals with dementia and examines five areas: Mood-Related Signs, Behavioral Disturbances, Physical Signs, Cyclic Functions, and Ideational Disturbances [41].

(6) Geriatric Depression Scale (GDS) Short Form. We are also examining depression using the GDS Short Form, a well-known screen for depression in older adults which is widely used in community and LTC settings [42,43].

(7) Revised Memory and Behavior Problems Checklist (RMBPC). Behavioral problems will be assessed using the RMBPC, a valid and reliable 24-item measure for people with dementia, that includes three subscales, Memory-Related Problems, Affective Distress, and Disruptive Behaviour [44].

(8) Short Portable Mental Status Questionnaire [45]. The Short Portable Mental Status Questionnaire (SPMSQ) is a 10-item examination that has been found reliable and valid in distinguishing demented subjects from cognitively intact subjects. It is quick to administer and does not require much training, and we are using the SPMSQ to assess mental status.

(9) Coloured Analogue Scale [46]. This scale is being used to assess pain via patient self-report. Specifically, pain is rated by moving a plastic glide along a 14.5 cm long grid, varying in colour and width. That is, the scale is 1 cm wide at the bottom gradually widening to 3 cm at the top. Its colour is light pink at the bottom and progresses to a deep red colour at the top. The ends of the scale are anchored by the polar opposites “no pain” and “most pain”. As such, participants are presented with several visible cues for scaling the severity of their pain: length, width, colour and the anchoring words. The back of the scale has numbers ranging from 0 to 10 that are used by the assessor for the recording of pain intensity. This measure has been shown to be a valid index of self-reported pain with seniors who have mild to moderate dementia in that scores increase from baseline to painful situations [47].

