### Data analysis

We hypothesize that participants taking part in the walking program will demonstrate maximal benefits compared to the no treatment control group (usual care) and the participants receiving only social interaction. We hypothesize that benefits of the walking program will include decreased fall rates, and improved balance, endurance, strength, mood, behaviour, activities of daily living and quality of life indices. As research has found that pleasant activities improve resident mood [54], we also hypothesize that participants in the social interaction group will demonstrate improvements in mood and other indices of quality of life.

The data will be analyzed using a random-effects multiple regression model [55]. The between-subjects factor will be condition (i.e., treatment and two control conditions). A random intercept for time (i.e., 5 measurement occasions) will be included to account for within-subject variation due to the repeated measurements. We will also evaluate model fit when a random slope for time is included in the model. Model fit will also be evaluated when the time x group interaction is included in the model. Additional covariates that may be included in the model are clinical measures from the RAI-MDS, such as the presence of comorbid conditions. Evaluation of model fit will be conducted using likelihood ratio tests and the Aikake Information Criterion [55]. Proportions of participants in the number of fall categories (e.g., non-faller, one-time faller, multiple faller) will be assessed using Pearson’s chi-square statistics.

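### Baseline cognition should be a fixed term in the outcome models, and the Data analysis and Other data collection sections should agree on it

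*Protocol article*

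**What the plan says.** - **Abstract, Methods/design.** The analysis is to take account of the longitudinal data and of "the potential for missing data points due to attrition".
- **Discussion.** Most recruits are expected to have some cognitive impairment, and "difficulty with data collection, in particular with those with severe impairments, is expected". No missingness rate is given, overall by cognition or by arm.
- **Data analysis.** The firm terms of the random-effects regression are condition and a random intercept over five occasions. A random slope and the group-by-time term are to be examined for fit. On covariates: "Additional covariates that may be included in the model are clinical measures from the RAI-MDS, such as the presence of comorbid conditions". Likelihood ratio tests and AIC are then named as the way to evaluate fit. Cognition is not mentioned.
- **Other data collection.** To control for confounding and to describe the sample, a list of RAI-MDS items is to enter the analysis. The list contains the Cognitive Performance Scale, and the wording is firm rather than permissive.
- **Outcome measures and Procedures.** Cognition is also measured directly ("we are using the SPMSQ to assess mental status"), at a baseline assessment held before allocation. The SPMSQ appears only as an outcome.

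**The concern.** A likelihood-based mixed model handles dropout validly when missingness depends only on what the model contains: observed outcomes and included covariates. If cognition predicts both dropout and the course of the outcome, leaving it out can break that condition. Likelihood ratio tests and AIC ask whether a term improves the fit to the observed outcomes. They do not ask whether it is needed for the missing-data assumption, so they are a poor basis for keeping or dropping a predictor of dropout.

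Two things are at stake. One is precision, since cognition is likely to be prognostic. The other is bias in the walking contrast if impaired residents are lost more often from one arm. Meanwhile the two sections that govern covariates give different answers on whether a cognition measure is in the model.

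**Working it through.** **The plan's own figures.** The Sample size section "assumed a moderate standardized effect size of 0.40", with an intra-class correlation of 0.05 and "α = .05, power = .80", and states 129 participants plus 50 for attrition. The 129 cannot be confirmed from these inputs. A standardized mean difference of 0.40 (two-sided) needs 99 per arm. An ANOVA effect size f of 0.40 with three groups needs 66 in total, and 66 × (1 + 19 × 0.05) = 66 × 1.95 = 128.7, but only if 20 residents per unit are assumed. The present point does not depend on this figure; it means only that comparisons with 0.40 below read it as a mean difference. The attrition allowance is 50/179 = 27.9%.

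**Assumed inputs.** The protocol gives no rates, so all of these are assumptions: 40% severely impaired and, where a within-person correlation is stated, 0.6. Positive bias favours walking.

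**A. Bias, walking against usual care.** Five occasions, random-intercept generalised least squares with known variance components, true effect zero, 20 runs of 20,000 per arm. Dropout is 50% in impaired walkers and 15% in everyone else. Month-4 group-by-time contrast, in SD:

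| Impaired start lower by | Further decline by month 4 | No cognition | Main effect only | With visit interaction |
|---|---|---|---|---|
| 0.5 | 0 | +0.015 | −0.003 | −0.002 |
| 0.8 | 0 | +0.027 | +0.002 | +0.002 |
| 0.5 | 0.2 | +0.037 | +0.016 | −0.001 |
| 0.5 | 0.4 | +0.060 | +0.034 | −0.001 |
| 0.8 | 0.4 | +0.068 | +0.035 | +0.002 |
| 0.8 | 0.8 | +0.108 | +0.066 | −0.003 |

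With 50% dropout of impaired residents in both arms, bias without cognition is within 0.003 in every row.

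Hand check: the impaired share still observed among walkers is 0.40 × 0.50 / (0.40 × 0.50 + 0.60 × 0.85) = 0.20/0.71 = 0.282, against 0.40 in usual care. The gap of 0.118 times a further decline of 0.2, 0.4 or 0.8 SD gives 0.024, 0.047 or 0.095. The rest of the simulated bias is of the size seen in the level-only rows.

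**B. Other loss patterns.** Visits at 0, 2 and 4 months, 60 per arm, 3,000 to 4,000 trials per setting:
- Further decline 0.5 to 0.8 SD, severe-group loss 50% to 60% in walking against 30% in usual care, 10% in others: bias 0.04 to 0.08 SD. A repeat with random-intercept least squares gave 0.036 to 0.098; with a cognition main effect only, 0.025 to 0.070; with the visit interaction, within 0.005 of zero.
- Further decline 0.5 to 0.8 SD, loss 40% against 30%: 0.02 to 0.03 SD.
- Further decline 0 to 0.2 SD, loss 55% against 30%: about 0.01 to 0.03 SD, against a standard error of about 0.18.

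**C. Precision.**
- *Group main effect*, setting A rescaled to 129/3 = 43 per arm: standard error 0.190 to 0.203 without cognition, 0.183 to 0.184 with it. Ratios run from 0.190/0.183 = 1.04 to 0.203/0.184 = 1.10.
- *Month-4 change contrast*, equal loss of 40% of severe residents and 10% of others: adding cognition cuts the empirical variance by 5% to 17% when the further decline is 0.5 to 0.8 SD. For a further decline of 0 to 0.2 SD the change in variance is between about −2% and +1%.

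Hand check, using only baseline and month 4: the impaired share observed is 0.24/(0.24 + 0.54) = 0.308, so its variance is 0.308 × 0.692 = 0.213. The change score has variance 2 × (1 − 0.6) = 0.80 within cognition groups. The share of variance due to cognition is 0.5² × 0.213 / (0.80 + 0.053) = 6%; for 0.8 SD, 0.136/0.936 = 15%; for 0.2 SD, 0.0085/0.8085 = 1%.

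The model-based standard errors of the change contrast in A (0.213 to 0.220) hardly move when cognition is added. They use variance components that leave out differential decline, so they cannot show this loss.

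**The case against.** - **Cognition is already in.** A reader might infer that cognition is left out or is merely optional. The Other data collection section does not support that, since it lists the Cognitive Performance Scale among data entering the analysis. This stands. But that section also serves to describe the sample and specifies no model term, and the Data analysis section is permissive. What remains is a mismatch to settle.
- **The protocol does not say missing data will concentrate in impaired residents.** It expects difficulty in collecting data. Where it discusses attrition it names refusal, inability to continue, morbidity and mortality. Eligibility requires following simple instructions, which narrows the group. This stands: concentrated missingness is a reasonable inference only.
- **Nothing predicts loss that differs by arm.** One might argue that walking five days a week asks more of impaired residents. But that bears on adherence, while assessments are scheduled alike in all arms, and a resident can stop walking and still be assessed. This stands, so the bias is conditional.
- **Fit selection of covariates is partly a reading.** Fit is tied expressly to the random slope and the interaction; the sentence on likelihood ratio tests and AIC is general. Fair, but no other rule for covariates is given.
- **This is detail for the analysis plan.** An article may leave the covariate list open. Here, however, it states a permissive rule in one section and a firm one in another, and neither fixes the term that matters for missing data.

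**Conclusion.** The point holds as a nearly free improvement, not as an error that undermines the trial. The general claim that the model loses precision is too strong. Omitting cognition makes the standard error of the group main effect about 4% to 10% larger. On the month-4 change contrast it costs about 5% to 17% of variance only if impaired residents also decline faster by an assumed 0.5 to 0.8 SD, and about nothing at 0 to 0.2 SD.

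The claim that the walking contrast will be biased is not supported either. Bias is about zero with equal loss. If loss of impaired residents is higher in the walking arm, it is about 0.01 to 0.11 SD in favour of walking: 0.01/0.40 = 2.5% to 0.11/0.40 = 27.5% of the planned effect, read as a mean difference. The upper end needs a further decline of 0.8 SD and 50% against 15% dropout. All these sizes rest on assumed inputs, because the protocol gives none.

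What does not depend on them is that fit statistics are the wrong test for this covariate, and that the two sections need aligning.

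**What to change.** Prespecify one baseline cognition measure taken before allocation: the SPMSQ, or the Cognitive Performance Scale already listed under Other data collection (using an assessment that predates allocation). Enter it and its interaction with visit as fixed terms in every outcome model, retained regardless of likelihood ratio tests or AIC. Where the SPMSQ is itself the outcome, its own baseline value serves. The interaction matters: a main effect alone leaves bias when cognition also drives decline. Other RAI-MDS covariates can stay optional. Reword Data analysis and Other data collection so that both say the same.

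The cost is wording and a few degrees of freedom: with a linear score and five occasions, one main effect plus four interaction terms, so at most five. No new data are needed.

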## Conclusion

Despite the challenges, through this study, insights may be garnered regarding benefits of a walking program and practical intervention implication insights. Determining if the intervention is beneficial may facilitate improved adherence with walking programs in LTC facilities. Improved resident quality of life, psychosocial function, functional abilities and fewer falls all have the potential to lead to favourable financial and health care system outcomes over the longer term.

## Abbreviations

ADL: Activities of daily living; BBS: Berg Balance Scale; CSDD: Cornell Scale for Depression in Dementia; GDS: Geriatric Depression Scale; LTC: Long-term care; OARS: Older American Resource Services; RA: Research assistant; RAI-MDS: Resident Assessment Instrument-Minimum Data Set; RMBPC: Revised Memory and Behaviour Problems Checklist; SDM: Substitute decision-maker; SFT: Seniors Fitness Test; SPMSQ: Short Portable Mental Status Questionnaire.
